### Timing of exams and procedures

#### Screening phase

The screening phase of the study will begin after signing of the informed consent and it will consist on the evaluation of the inclusion and exclusion criteria and in the collection of a venous blood sample (10 ml) for the determination of the FcγR polymorphisms. Baseline visit and exams will be carried out within 21 days before therapy start (clinical history, clinical examination, PS ECOG, vital signs) along with the beyond described parameters. Blood count and clinical biochemistry will be performed at our local laboratories. The following variables will be evaluated: hemoglobin, blood count with leukocyte formula, platelets, total bilirurbin, AST, ALT, alkaline phosphatase, serum creatinine, total proteins, sodium, potassium, calcium, urea, lactic dehydrogenase, creatinine clearance, CEA and CA19.9. ECG and cardiac ultrasonography with evaluation of the ventricular ejection fraction will be also performed. Pregnancy test will be done for all potentially childbearing women and must be negative during the screening phase. The test can also be repeated during treatment if requested by the local Ethics Committee. All patients, throughout the duration of the study, must use barrier methods for anti-conception. Total-body Computed Tomography with iv contrast or, if contraindicated, Magnetic Resonance (MRI) abdomen and chest computed tomography without iv contrast will be obtained.

#### Treatment phase

Clinical examination, evaluation of vital signs, blood count and clinical biochemistry will be performed at day 1 of each cycle before administration of folfiri/cetuximab (every 2 weeks). Cardiological evaluation, CEA, CA19.9 and assessment of response to treatment will be performed after 3 months of therapy start and thereafter every 3 months until progression.

#### End-of-treatment phase

The suspension of the treatment can occur in case of toxicity, progression, and/or at the request of the patient. Additional treatment lines or follow-up procedures will be applied at the discretion of the clinician responsible of the medical treatment. The final visit will be made immediately after disease progression. The following data will be collected: ECOG Performance Status, clinical examination, vital signs, blood count and clinical biochemistry. The end of study visit should be done within 30 days of the last administration of folfiri/cetuximab and before starting any second-line CT. The cutaneous toxicity, if present, will be followed-up until resolution; if second-line CT will be undertaken the treatment will not start before its resolution. In any case, the outcome of adverse events will be recorded after the the end of study visit. The “patient death form” must be completed when the patient dies. The end-of-study form should be completed for patients who die before the end of study visit and if the patient withdraws consent, preferably before 28–32 days after the last folfiri/cetuximab administration.

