### Duration of therapy

Administration of folfiri/cetuximab will be allowed until progression or unacceptable toxicity. In case of unacceptable toxicity related to irinotecan the patients will continue cetuximab and 5-FU until progression. In case of unacceptable toxicity related to cetuximab the patient will continue folfiri until progression. In case of unacceptable toxicity related to 5-FU the patients will continue with cetuximab and irinotecan until progression.

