### Dose modifications for folfiri

Dose reductions wil be applied in relation to the more severe side effect. Once modified, the dose of the drug will be the same for the subsequent cycles. A 20% reduction of folfiri will be permitted in case of grade ≥ 3 of haematologic or non-haematologic toxicities (except for alopecia). Folfiri will be rechallenged after *recovery* of toxicity to baseline or *grade 1* or less. At the second appearance of grade ≥ 3 side effects a dose reduction of 50% will be applied; after a further grade ≥ 3 toxicity or after the first appearance of grade ≥ 2 cardio-vascular chemotherapy will be permanently discontinued. Chemotherapy will also be interrupted in case of postponement of the administration for more than 4 weeks. No prophylactic use of G-CSF o erythropoetin is planned.

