### Dose modifications for cetuximab

Cetuximab infusion will be delayed in case of grade > 3 cutaneous toxicity for 2 weeks. The investigator will also consider the administration of topical and/or oral antibiotic drugs and/or topical corticosteroids [30]. The treatment will be reintroduced if the cutaneous toxicity reduces to grade 2 or lower. If grade 3 skin toxicity reoccurs at a second or third time, cetuximab will be postponed for a further 2 weeks, but when reintroduced the dose will be reduced to 200 mg/mq and 150 mg/mq, respectively. Dose reductions of cetuximab are permanent and it will be permanently discontinued in case of 4 weeks suspension or fourth grade 3 toxicity event occurrence despite appropriate dose adjustments. Allergic reactions may occur during or after administration of cetuximab. In case of allergic reaction, the patient will be treated according to clinical practice. The patient should also be asked to report immediately to the doctor if any late reaction occurs. In case of grade 1 allergic reaction the cetuximab infusion rate will be reduced at 50%; it will not be increased subsequently, but rather reduced at any subsequent administration. In case of a second allergic or hypersensitive reaction despite the reduced infusion rate, the infusion will be interrupted and the patient will continue with folfiri alone. If the patient experiences an allergic or hypersensitive reaction of grade > 3, cetuximab will be permanently discontinued and chemotherapy will be continued if considered appropriate by the investigator.

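### The end-of-treatment rule holds second-line chemotherapy for any unresolved skin toxicity, however mild

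*Protocol article*

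**What the plan says.** The rule stands in the protocol article under End-of-treatment phase. Skin toxicity that is present is to be followed until it resolves, and "if second-line CT will be undertaken the treatment will not start before its resolution". The condition applies to any skin toxicity: no grade, time limit or exception is attached.

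Two other sentences in that section bear on it. An earlier one says: "Additional treatment lines or follow-up procedures will be applied at the discretion of the clinician responsible of the medical treatment". A later one says: "In any case, the outcome of adverse events will be recorded after the the end of study visit".

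The on-study rules are in three other sections:

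- **Duration of therapy:** "Administration of folfiri/cetuximab will be allowed until progression or unacceptable toxicity".
- **Dose modifications for folfiri:** "A 20% reduction of folfiri will be permitted in case of grade ≥ 3 of haematologic or non-haematologic toxicities", with alopecia excepted, and "Folfiri will be rechallenged after *recovery* of toxicity to baseline or *grade 1* or less".
- **Dose modifications for cetuximab:** "Cetuximab infusion will be delayed in case of grade > 3 cutaneous toxicity for 2 weeks", and "The treatment will be reintroduced if the cutaneous toxicity reduces to grade 2 or lower". The sentences that follow speak of grade 3 recurrences, so the trigger may be meant as grade 3 or higher. Under either reading, grade 1 or 2 is below it.

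**The concern.** Study treatment may run until progression, so some patients can be expected to need second-line chemotherapy while they still have a rash. For them the end-of-treatment rule is mandatory as written. A site that follows it literally withholds the next chemotherapy from a patient with progressing metastatic disease because of a rash that, the day before, might have been no reason to withhold treatment.

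What is at stake is the timing of care after progression. The trial's own data do not appear to need the hold. The section on response and toxicity assessment reports the maximum grade per patient and counts a repeated event once. The end-of-treatment section already asks for the end-of-study visit before second-line treatment starts, and for adverse-event outcomes to be recorded after that visit.

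**Working it through.** No figure in the article can be reproduced or recomputed here, so the check is a comparison of rules.

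**Step 1. What counts as resolved?** The article does not define it. The toxicity section describes grade 0 as absence of the event, so grade 0 is the ordinary reading (reading A). A looser reading is grade 1 or less (reading B).

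**Step 2. Apply each rule to each kind of residual rash.** The on-study columns ask whether the rash alone would hold that treatment.

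| Rash when the next treatment is due | Folfiri on study | Cetuximab on study | Second-line, reading A | Second-line, reading B |
|---|---|---|---|---|
| Grade 1, never above grade 2 | not held | not held | held | not held |
| Grade 2, never above grade 2 | not held | not held | held | held |
| Grade 1, after grade 3 or higher | not held (rechallenge limit met) | not held | held | not held |
| Grade 2, after grade 3 or higher | held (rechallenge needs grade 1 or less) | not held (restart limit met) | held | held |
| Grade 3 or higher, unresolved | held | held (at grade 3, if the trigger includes grade 3) | held | held |

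**Step 3. Read off the excess.** Under reading A, the end-of-treatment rule is stricter than both on-study rules in the first three rows. Under reading B, it is stricter than both only in the second row. In the fourth row it agrees with the folfiri rule and is stricter only than the cetuximab rule. So the rule is too strict for at least one common-sense case under either reading, and for three under the ordinary one.

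**Step 4. Does the discretion sentence create an exception?** It is general and comes first. The resolution rule is specific, comes later and is worded as a requirement. Nothing links the two, so the discretion is not written as an exception.

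**Step 5. Can the delay be sized?** This would need the share of patients with rash at progression and the time from then to resolution. The article gives neither, so no count of patients or weeks follows.

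**The case against.** The strongest reply is that the harm turns on one undefined word in a condensed article. The full protocol may define resolution as recovery to grade 1 or less, which would match the article's own limit for restarting chemotherapy. That narrows the point, but a grade 2 rash that was never worse would still be held. The restriction itself is also printed as an operative rule, so the concern is not about missing detail.

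A second reply is that the hold may be deliberate, either as a cautious washout or to keep skin events attributable to study treatment. The attribution argument has some force and is the real cost of relaxing the rule. It is weakened because toxicity is summarised by maximum grade.

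A third reply is that later lines are left to the clinician, so the section was perhaps never meant to override clinical judgement. If so, the clause misstates the intent and still needs correcting.

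Some stronger readings are tempting, and the article does not support them:

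- **That every grade 1 or 2 rash would have been treated through on study.** A grade 2 residue of a grade 3 or higher event would still hold folfiri.
- **That the rules contradict each other.** They govern different decisions: modifying study drugs, and starting a later line.
- **That the 26% rate of grade 3–4 skin reactions quoted from an earlier phase III trial shows how many patients are affected.** That rate describes severe reactions in another trial and says nothing about rash present at progression.

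**Conclusion.** The point holds as a minor patient-care matter and a cheap improvement. As worded, the rule can delay second-line chemotherapy for a rash that never exceeded grade 2, or for a grade 1 residue of a worse event, neither of which would hold folfiri or cetuximab on study. The grade 1 cases depend on taking resolution to mean complete disappearance. The case of a grade 2 rash that was never worse does not depend on that.

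The number of patients and the length of delay cannot be given. The trial's inference is unaffected: response, PFS and the two-stage design (14 then 34 patients) do not depend on when second-line treatment starts after progression. A reader might infer that overall survival would be distorted. A delay could in principle bear on it, but it is a secondary endpoint in a single-arm trial and the article offers no basis for sizing an effect.

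**What to change.** In the End-of-treatment phase section, replace the clause that makes second-line chemotherapy wait for resolution with wording such as:

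*Skin toxicity that reached grade 3 or higher delays second-line chemotherapy until it has recovered to grade 1 or less, or until an earlier time chosen at the treating clinician's discretion. Skin toxicity that never exceeded grade 2 does not delay it. Skin toxicity is followed to resolution, including during later therapy.*

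The grade 1 limit is the article's own threshold for restarting chemotherapy. It suits this decision better than the grade 2 limit, which was set for restarting cetuximab.

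The cost is the rewording of one clause. Sample size, the response cut-offs, alpha (5%) and power (95%) stay as they are. The downside is that skin outcomes recorded after second-line treatment begins may partly reflect the new regimen. Recording the start date of second-line treatment alongside those outcomes would let them be read with that in mind.

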### Response and toxicity assessment

The assessment of response will be perfomed through total-body computed tomography with iv contrast (if contraindicated: abdomen MRI and chest computed tomography without iv contrast), CEA and CA19.9 after 3 months of folfiri/cetuximab and every 3 months thereafter until progression. Responses will be classified according to the RECIST v. 1.1. An independent blinded central review of radiologic examinations will be performed by a DMC (Data Monitoring Committee). The independent DMC will be also responsible of reviewing the PFS data. Toxicity will be assessed in accordance with the CTCAE, version 4.0. The CTCAE contains 26 categories of adverse events, organized for pathophysiology, anatomy and etiology. Each adverse event is graded with a scale ranging from 0 (absence of event or value within the normal range) to 5 (death caused by the adverse event). Patients will be assessed for the presence of adverse events at each study visit and will also notify the investigator by telephone in case of significant adverse events reported between one visit and the next. For each adverse event, the maximum grade per patient will be reported. If a patient experiences a toxic effect of any grade on multiple occasions, the event will be counted only once.

### Translational research

Biomarkers will be evaluated in specimens and correlated with outcomes and therapy effectiveness. In particular, the primary tissues, and metastases when available, will be characterized for the presence of tumor-infiltrating M2 macrophages by immunohistochemistry through the expression of CD163 (ab182422, Abcam), TGF-β (ab92486, Abcam), Arginase-1 (GTX113131, Genetex), SSP1 Osteopontin antibody (ab218237, Abcam], and PD-L1 (E1L3N®, XP®). M1 infiltrating macrophages will be detected through the following antibodies: CD86 (ab53004, Abcam), iNOS (ab115819, Abcam), IFN-γ (ab218426, Abcam), TNF (ab1793, Abcam). Natural Killer (NK) and Cytotoxic T Lymphocites (CTL) will be characterized as follows: NKP46+ (Clone 195,314, R&D system), granzymeB (ab134933, Abcam), Foxp3+ (ab20034, Abcam). For FcγR polymorphisms detection, DNA will be extracted from the whole blood lymphomonocyte component of each patient (10 ml of venous blood) by Ficoll-Paque density gradient. The analysis of the V158F and H131R alleles will involve a gene amplification phase by PCR reaction with oligonucleotides specific for the regions of interest and a subsequent PCR products analysis by automatic sequencing (Big Dye terminators version 3.1 cycle sequencing kit and 3130 Genetic Analyzer; Applied Biosystems) [20, 21]. As an internal quality control, samples with previously known sequenced genotype will be used. These investigations will be conducted in the laboratories of the “Cellular biology and biotherapies Unit” of the National Cancer Institute of Naples, IRCCS “G. Pascale”.

To study cetuximab-mediated ADCC, peripheral blood mononuclear cells (PBMC) from patients will be isolated at diagnosis by Ficoll-Paque Plus gradient centrifugation (GE Healthcare), then they will be cultured in complete RPMI-1640 medium enriched with human IL2 (10 ng/mL) for 18 h in order to generate Lymphokine-Activated Killer (LAK) cells. Target CRC cells (HT29) will be plated in a 96-well plate at 1 × 10^4^ cells/well. Twenty-four hours later, LAK will be added at a 10:1 effector:target (E:T) ratio in fresh medium, in the presence of cetuximab (10 μg/mL), or the rituximab (anti-CD20, 10 μg/mL), as negative control, or in the presence of staphylococcal enterotoxin B (SEB) as positive control. Cytotoxicity will be evaluated by sulforhodamine B (SRB) assay [31]. ADCC elicited by not activated freshly prepared PBMCs will be also evaluated at E:T cell concentration ratios of 20:1 and 10:1. The specific cytolysis percentage will be calculated using the following formula: Cytotoxicity (%) = [1 − (mean test optical density/mean optical density target)] × 100 [32, 33]. Cetuximab-mediated ADCC is given by cytotoxicity_with cetuximab_ − cytotoxicity_without cetuximab_. All experiments will be performed in triplicate, and results expressed as mean values ± standard error. These investigations will be conducted in the laboratories of the “Functional Genomics” of the National Cancer Institute of Naples, IRCCS “G. Pascale”.

## Discussion

The identification of predictive biomarkers characterizing the ideal treatment of mCRC patients is subject of intense investigation. RAS oncogenes in mCRC have not completely satisfied this unmet need since about 40% of patients with RAS wt mCRC dose not respond to anti-EGFR treatments. We previously reported in a series of 74 KRAS wt mCRC patients, genotypic frequencies of FcγRIIIa and FcγRIIa of 36% VV, 54% VF, 10% FF and 36% HH, 56% HR, 8% RR, respectively; interestingly, FcγRIIIa but not FcγRIIa polymorphisms were significantly associated with response to anti-EGFR-based therapy [20]. FcγRIIIa polymorphisms had also significant prognostic value for PFS [FcγRIIIa: median PFS 18.2 months in V/V patients (18 patients, 13 events) vs 17.3 months in V/F patients (26 patients, 25 events) vs 9.4 months in F/F patients (5 patients, 5 events); Log Rank test: *p* = 0.04] at univariate and multivariate analyses (HR: 2.35; CI: 1.37–4.01; *p* = 0.001) with grading and response to first-line chemotherapy. In another study, we described genotipic frequencies of FcγRIIa and IIIa in 96 consecutive mCRC patients and 148 control subjects and we analyzed the clinical impact of cetuximab-mediated ADCC in vitro from LAK patients-derived [21]. There were no statistically significant differences between the control and study groups in terms of genotypic frequencies. The incidence of FcγRIIIa V/V, V/F and F/F were: 28, 47 and 23%, respectively. Interstingly, the FcγRIIIa V/V and V/F genotypes were associated with higher cetuximab-mediated ADCC compared with F/F, median 27% (range: 0–76%) and 20% (0–57%) versus 9% (0–36%), respectively (*p* = 0.001). The response rate was higher in patients with the FcγRIIIa V allele (*V/V and V/F* genotypes) compared with the F/F genotype (*p* = 0.025) as well as the PFS of patients with FcγRIIIa V/V and V/F was significantly longer than that of patients with F/F (10.8 vs. 5.1 months respectively, *p* = 0.05, Log Rank test). The extent of in vitro cetuximab-mediated ADCC was significantly correlated with cetuximab clinical response (30% in responders vs 8% in non-responders patients, *p* = 0.020; ANOVA test). These observations prompted us to prospectively design the CIFRA trial, which is an investigator initiated phase II study to verify a superior activity of folfiri/cetuximab of 70% (+ 10% of that previously described) in mCRC patients selected on a genetic polymorphism of FcγRIIIa. The risk of a possible unexpected detrimental effect in this selected population is reduced in CIFRA study by the two-stage design that will stop the enrollment early if the first condition of acceptable activity is not met.

Notably, the CIFRA study will also prospectively address whether the ADCC phenomenon contributes to cetuximab activity. The hypothesis of ADCC as additional or alternative anti-cancer mechanism is supported by two mirror observations: i) a small percent of KRAS mutated mCRC patients respond to cetuximab [34, 35] and, ii) not all “all RAS” wt mCRC patients respond to anti-EGFR therapy [35]. Thus, blockade of signal transduction may not be the only mechanism of action resulting in the clinical benefit of cetuximab [36]. In fact, ADCC induced by EGFR-specific mAbs may inhibit tumor progression in vivo, even in cancers resistant to EGFR signaling inhibition [37]. Immune mechanisms besides molecular alterations, could contribute to cetuximab activity as suggested also by indirect data of Seo and colleagues [38] who reported a significant correlation between EGFR expression and ADCC activity, but not with the mutational status of RAS and BRAF. To this regard, CIFRA results could prompt a clinical pilot study to test the activity of cetuximab-based therapy in RAS mutated FcγRIIIa V/V mCRC patients. Additionally, CIFRA may suggest a more complex evaluation including FcγRIIIa polymorphisms and prompt phase III studies in order to compare panitumumab versus cetuximab with folfiri in RAS wt/FcγRIIIa V/V mCRC patients.

Furthermore, TM characterization (i.e. NK cells, M1 vs M2 macrophages) and cetuximab-mediated ADCC will help to understand any relation between specific signaling pathways and treatment response, as recently reported [39, 40]. Although the description of complex TM biology or dynamics is beyond the scope of this article, herein TM will be evaluated with particular regard to tumor-associated macrophages (TAM), the most represented tumor-infiltrating host cells (may represent up to 50% of the tumor mass). TAM are classically distinct in activated (M1) macrophages and alternatively activated (M2) macrophages [41]. M2 TAMs can produce growth factors and cytokines such as CCL2, CXCL12, CXCR4, TGFβ, VEGF, PDGF, COX-2 and metalloproteinases that determine immunesuppression and stimulate local tumor growth as well as the metastatic process [42–44]. NK cells-mediated ADCC is reduced by M2 TAMs through TGFβ release and induction of a CD27^low^CD11b^high^ NK phenotype [45]. Conversly, M1 TAMs stimulate anti-tumor CD4^+^ and CD8^+^ T cells response and also interact with NK cells that produce IFN-γ to amplify anti-tumor activity [46, 47]. However, the role of TAMs during tumor progression and response to anti-cancer therapies is still under investigation. Interestingly, TAMs express both FcγRIIa and IIIA, but the differential role of M1 vs M2 during administration of therapeutic antibodies remains undetermined. Data from TAM characterization could help to interpret CIFRA results as well as provide new insights in TM interactions and cetuximab activity. In selected patients, cetuximab could be managed as an “immunotherapeutic drug” and association with NK-activating cytokines (IFNs, IL-2) [48] could also gain relevance in the attempt to activate ADCC against antibody-coated cancer cells.

